### Screening and Baseline Assessment

Following registration and informed consent, potential participants are issued a set of screening questionnaires.

#### Demographics

Demographics include: current country of residence, age, sex, and highest attained educational level using the categories used by Statistics Norway*.* Participants will be excluded if they do not indicate that they live in Norway or if they indicate an age <16 years.

#### Previous Use of Self-Help Apps for Mental Health

A list of mobile phone–based self-help apps available for use in Norway will be provided along with instructions to check any that have been used in the past. A tentative list can be found in Multimedia Appendix 3, which will be updated shortly prior to recruitment. Participants will be excluded if they indicate that they have previously used Tankevirus or Grubl.

#### Current Level of Anxiety and Depression

Current level of anxiety and depression will be measured using the GAD-7 and the PHQ-9. Participants will be excluded if they report a total PHQ-9 score ≥20, indicating severe depression; if they report a score ≥2 on PHQ-9 item 9, indicating active suicidal ideation; or if they report a total score ≤4 on both GAD-7 and PHQ-9, indicating that they do not have at least mild levels of either anxiety or depression.

#### Questions Regarding Current and Past Health Care Use for Mental Health Issues

Participants will be asked whether they have at any point in the past required mental health care of different types, and will be asked to check any in a list of different types of health services they have used in the past, including follow-up from general practitioner; having seen a psychologist or psychiatrist; and having required hospitalization.

Participants will be asked whether they currently receive any mental health support and will be asked to check any that are relevant from a list. Participants will be excluded if they indicate that they are currently being treated for mental health issues or if they indicate that they have previously required hospitalization for mental health issues.

Excluded individuals will be thanked for their interest and informed of the reason for exclusion. Participants indicating severe depression (PHQ-9 ≥20) or responding with a score of ≥2 on PHQ-9 item 9, suggesting suicidal ideation, will also be provided with information on where they can seek help. Draft information to be provided is available in Multimedia Appendix 4. Individuals excluded based on other criteria will be provided with links to public information on mental health and links to the regular Tankevirus and Grubl apps. All excluded individuals will be informed that all the information provided will be deleted once recruitment is complete.

Given the financial incentive provided, there is a risk of individuals attempting duplicate participation. While this cannot fully be ruled out, the risk is limited by use of phone number and full name at registration.

Eligible participants will be asked to complete remaining baseline questionnaires before randomization.

Participants are informed that they will have the option to move on to another treatment option following closure of the data collection.

#### Randomization

Participants are randomized in a 1:1:1 ratio to Tankevirus, Grubl, or the placebo condition.

#### Treatment Phase

Participants follow the Tankevirus, Grubl, or placebo app for the full duration, with automatic reminders in the form of notifications.

#### Postintervention Follow-Up

Upon completion of the last program element or after 4 weeks, participants will be invited to respond to the postintervention follow-up. This comprises all clinical questionnaires (PHQ-9, GAD-7, EQ-5D-5L, and WSAS), retrospective health care resource use over the last 4 weeks, questions about co-occurring treatment, SUS, and the CSQ-8.

Participants who have not submitted any outcome assessment within 2 weeks of the scheduled assessment date, despite automated push notification reminders, will be considered lost to follow-up for that time point. This rule applies at postintervention and at 3- and 6-month follow-up.

#### 3-Month Follow-Up

Participants are administered all clinical questionnaires (PHQ-9, GAD-7, EQ-5D-5L, and WSAS), retrospective health care resource use since the postintervention follow up, and questions about co-occurring treatment.

#### 6-Month Follow-Up

Participants are administered all clinical questionnaires (PHQ-9, GAD-7, EQ-5D-5L, and WSAS), retrospective health care resource use since the 3-month follow-up, and questions about co-occurring treatment.

#### End of Trial

Completing participants are provided with an electronic gift card voucher valued at NOK 500 (approximately US $50). This is tentative; another option is to provide each participant with 2 gift cards valued at NOK 250 (approximately US $25); 1 following completion of the postintervention follow-up, and 1 following the 6-month follow-up. The completion criterion here is exclusively linked to response to questionnaires and not to the use or completion of app content.

### Safety Considerations

Use of MIND-APP is considered safe for users. Tankevirus and Grubl provide videos with psychoeducational contents, and the placebo app will include a set of short attention/concentration games to be done in a few minutes each day. Identifiable information is stored separately from recorded trial data. However, we cannot conclusively exclude the possibility that study participants experience discomfort while using the apps.

While the intervention type involved in MIND-APP is unlikely to be associated with most types of adverse events, monitoring is conducted as per clinical RCT conventions.

Adverse events are defined as any untoward medical occurrence in a participant to whom a medicinal intervention has been administered, including occurrences that are not necessarily caused by or related to that product. Serious adverse events are defined as any untoward medical occurrence that: results in death, is life-threatening, requires inpatient hospitalization or prolongation of existing hospitalization, results in persistent or significant disability/incapacity, or consists of a congenital anomaly or birth defect. The term “life-threatening” in the definition of “serious” refers to an event in which the participant was at risk of death at the time of the event; it does not refer to an event that hypothetically might have caused death if it were more severe.

Other “important medical events” may also be considered a serious adverse event when, based on appropriate medical judgement, the event may jeopardize the participant and may require medical or surgical intervention to prevent one of the outcomes listed above.

Participants may report potential adverse events via a dedicated menu option in the app or by contacting the trial team directly by phone or email. Adverse events will be collected systematically from randomization through the 6-month follow-up assessment.

While unlikely for most users, repeated self-monitoring or exposure to sensitive psychoeducational topics might prompt distress, anxiety, sadness, or increased rumination in some participants.

Self-monitoring could lead to heightened symptom awareness, possibly resulting in perceived or actual increases in distress.

Frustration, confusion, or distress could result from app malfunctions, usability challenges, or notification fatigue.

Worsened symptoms will be captured by the recording of symptoms in the trial. In addition, a menu item not present in the regular Tankevirus and Grubl apps will be provided, allowing users to report any discomfort and to optionally complete PHQ-9 and GAD-7 to report their current mental health. Users indicating severe depression (PHQ-9 score ≥20) or reporting score ≥2 on item 9 of PHQ-9, suggesting suicidal ideation, will be provided with information on where they can seek help (Multimedia Appendix 4).

The relationship of each adverse event to the intervention must be determined by a qualified individual according to the following definitions:

Unrelated: where an event is not considered to be related to the intervention.Possibly: although a relationship to the intervention cannot be completely ruled out, the nature of the event, the underlying disease, concomitant medication, or temporal relationship make other explanations possible.Probably: the temporal relationship and absence of a more likely explanation suggest the event could be related to the intervention.Definitely: the known effects of the intervention, its therapeutics class, or findings from challenge testing suggest that the intervention is the most likely cause.

All adverse events (serious adverse events) labeled possibly, probably, or definitely will be considered related to the intervention.

We do not anticipate that the study interventions (Tankevirus, Grubl, or the placebo app) should result in any adverse events but this section is included in case such events are reported so that they can be considered for causal links to the study. Only adverse events that are clinically judged by the research site monitoring board as being caused by the trial intervention will be reported in accordance with Akershus University Hospital guidelines. Participants will be asked at follow-up whether they have experienced any side effects or medical events while participating in the MIND-APP trial by way of a reporting option in the app. Participants may also report potential serious adverse events via phone or email correspondence with the trial team.

We do not anticipate any serious adverse events due to the digital interventions or data collection.

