### Interventions

#### Overview

No medication is administered within the study, nor are any medications prohibited.

Participants are also prohibited from using other self-help mental health smartphone apps during the 4-week intervention period. Adherence to this rule will be assessed at each follow-up time point via a dedicated question in the app. Concomitant psychological therapy is prohibited during the 4-week intervention period but is permitted during the 3- and 6-month follow-up phases; its use will be recorded as a potential covariate in sensitivity analyses.

Tankevirus and Grubl are 2 structurally similar self-help apps with different visual design, different lengths, and different contents. Shared characteristics include:

Onboarding with baseline measurement of mental health with feedbackPsychoeducational videosA set of shorter videos and tasks delivered 1 each day following the introductory videosMental health measurement following completion, with feedback on self-reported changeLong-term follow-up measurement at 3 and 6 monthsAutomatic reminders (daily push notifications)Program progress trackingOptions to rewatch elements of particular interest

The regular versions of Tankevirus and Grubl use a set of standardized questionnaires used to track mental health, specifically the Patient Health Questionnaire-4 (PHQ-4) inventory, which comprises 2 questions from the PHQ-9, covering depression, and 2 questions from the GAD-7, covering anxiety; the Somatic Symptom Scale 8-item (SSS-8); and a visual analogue scale inspired by the one used in the EQ-5D family of instruments. In the MIND-APP implementation, these are substituted by the longer PHQ-9 and GAD-7 instruments, and the full EQ-5D-5L.

The placebo condition will be designed to mimic these structural elements, with the exception of the content elements, as described below

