#### Secondary Outcomes

Secondary outcomes WSAS and EQ-VAS will be compared between baseline and the 3 primary follow-up time points (4-week, 3-month, and 6-month) in the same manner as the primary outcome.

EQ-5D-5L will be used to determine differences in accrual of QALYs between the trial arms using Norwegian population preference weights. The primary QALY analysis will include only the observed period, with separate analyses using extrapolation to 1- and 3-year time horizons.

The score on the EQ-5D-5L anxiety and depression dimension will be analyzed as a separate measure in the same way as the primary outcome.

The proportion of participants reporting worsened symptoms and treatment-emergent adverse events will also be compared.

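### The adverse-event definition does not fit an app trial, and the promised follow-up question on harms appears in no scheduled assessment, so the between-arm adverse-event comparison may rest on incomplete and unequal capture

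*Protocol article*

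**What the plan says.** Definition. Safety Considerations defines an adverse event as "any untoward medical occurrence in a participant to whom a medicinal intervention has been administered". The Interventions overview says "No medication is administered within the study". Safety Considerations also names the harms it thinks possible: repeated self-monitoring or sensitive content "might prompt distress, anxiety, sadness, or increased rumination in some participants", and app faults, poor usability or too many notifications may cause frustration or confusion.

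Collection. The same section states: "Adverse events will be collected systematically from randomization through the 6-month follow-up assessment". It offers a menu option, phone and email as routes that participants may use. It then says that participants will be asked at follow-up about side effects or medical events, "by way of a reporting option in the app". Risk Management and Participant Safety mentions a structured reporting system within the app.

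Schedule. The contents of the three follow-up assessments are itemised. The 3-month list, for example, consists of the clinical questionnaires, "retrospective health care resource use since the postintervention follow up, and questions about co-occurring treatment". The postintervention and 6-month lists, and Table 1, likewise have no adverse-event entry.

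Use. The Abstract counts adverse events among the secondary outcomes. Secondary Outcomes in the Statistical Analysis Plan says: "The proportion of participants reporting worsened symptoms and treatment-emergent adverse events will also be compared".

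**The concern.** A between-arm comparison of adverse events needs two things: a definition that tells every assessor what counts, and a way of asking that is the same in every arm. The article is unclear on both.

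The definition is drug-trial wording. It leaves open whether non-medical harms, which are the ones this trial is most likely to see, are events at all. The collection text promises a question that the schedule does not contain and attaches it to something that could be either a prompted item or a menu entry that waits to be opened.

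If it is the latter, what is recorded depends on a participant choosing to report. Participants know their app. The active programmes last 12 days (Grubl) and about 14 days (Tankevirus), while the collection window runs to 6 months. Willingness to open the app and report could then differ between arms for reasons unrelated to harm. A statement that an app caused no excess of adverse events would be poorly supported, and so would a statement that it did.

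**Working it through.** The article gives no adverse-event rate and no power for harms, so there is no figure to reproduce. The check sets the places side by side.

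| Question | Safety text | Other text | Result |
|---|---|---|---|
| What triggers the definition? | A medicinal intervention | Interventions overview: no medication is given | Wording does not fit any arm |
| Which harms count? | Medical occurrences | Same section foresees distress, rumination, frustration | Coverage of the expected harms is unclear |
| Is collection active? | Systematic; asked at follow-up | Asked through a reporting option; otherwise menu, phone, email | Prompted or passive is left open |
| Is the question scheduled? | Implied at follow-up | Table 1: no row. Postintervention, 3-month and 6-month lists: no item | Listed in 0 of 3 follow-up assessments |
| Is it an outcome? | Not stated | Abstract: secondary outcome. Secondary Outcomes under Assessments: not among the four listed. Statistical Analysis Plan: compared between arms | Status is inconsistent, but a comparison is planned |
| Which events are reported? | Only those judged caused by the intervention, under hospital guidelines | Statistical Analysis Plan: treatment-emergent events, with no causality limit | Scope of the rule needs stating |

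Table 1 does schedule satisfaction, usability and a co-treatment check. The harms question is therefore missing from a list that is otherwise detailed.

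**Illustration of incomplete capture.** The event rates are assumptions and do not come from the article: true adverse-event risks of 10% and 5%. The 300 per arm is from Sample Size Calculation. Let s be the share of events captured, equal in both arms, so p1 = 0.10s and p2 = 0.05s, with p̄ their mean. At two-sided α = .05,

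power = Φ{[(p1 − p2) − 1.96·√(2p̄(1 − p̄)/n)] / √([p1(1 − p1) + p2(1 − p2)]/n)}.

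- s = 1: (0.05 − 1.96 × 0.02151)/0.02141 = 0.367, power 64%
- s = 0.75: rates 7.5% and 3.75%, power 51%
- s = 0.5: (0.025 − 1.96 × 0.01551)/0.01548 = −0.349, power 36%
- s = 0.25: rates 2.5% and 1.25%, power 20%

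**Illustration of unequal capture.** Take a true risk of 10% in both arms. If 60% of events are captured in one arm and 30% in the other, the observed rates are 0.10 × 0.6 = 6% and 0.10 × 0.3 = 3%. The apparent difference of 3 percentage points is due to reporting alone. Swapping the capture rates reverses its sign, so the direction cannot be predicted.

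**The case against.** The strongest reply is that the article does promise to ask. Safety Considerations says participants will be asked at follow-up, calls collection systematic, and offers phone and email in addition. Compensation depends on answering questionnaires, not on using app content, so contact need not end with the programme. This reply stands in part. A reader might infer that adverse events are left wholly to volunteered reports, and that about 5 of the 6 months have no active collection. The article does not support that inference, because it holds only if the reporting option turns out to be passive. What the reply does not remove is the conflict between the promise and the itemised schedule.

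Second, the drug-trial definition is standard wording, and the section clearly means it to cover Tankevirus, Grubl and the placebo app. That is right. A reader might infer that no participant can ever have an adverse event. This follows only from a literal reading that the surrounding text rules out. The uncertainty about non-medical harms remains on a sensible reading too.

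Third, worsening is captured independently of these routes. PHQ-9, GAD-7, EQ-5D-5L and WSAS are scheduled in all arms, and a menu item lets users report discomfort and complete PHQ-9 and GAD-7 between assessments. This stands for the worsened-symptoms half of the planned comparison, which can still suffer from missing follow-up. It does not cover other harms.

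Fourth, an article may leave operational detail, such as how a reported admission becomes a safety record, to a fuller document. That is accepted, and no such omission is raised here. The point concerns statements in this article that do not agree with each other.

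**Conclusion.** The point holds as a definition that does not fit the trial and as an inconsistency between the safety text and the assessment schedule. It should be settled before launch. It is not shown that events will be under-counted. That is a risk, conditional on the in-app option being passive, and it applies only to the comparison of treatment-emergent adverse events.

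Its size cannot be derived from the article. The firm count is that none of the three itemised follow-up assessments, nor Table 1, lists an adverse-event item. The power figures rest on assumed event rates and show only that incomplete capture weakens the comparison considerably. The unequal-capture example shows only that a difference, or its absence, could be an artefact of reporting.

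The rule that only events judged caused by the intervention are reported may concern institutional reporting alone. If it also governed the analysis, the comparison would be filtered by a causality judgement, so the article should say which is meant.

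**What to change.** 1. In Safety Considerations, define an adverse event as any untoward physical or psychological occurrence in a randomised participant, whether or not related to the app. State that the risks named in that section are covered.
2. Reconcile Safety Considerations with Table 1 and the three follow-up descriptions. Schedule one prompted harms item, identical in all arms, at postintervention, 3 months and 6 months. In the Statistical Analysis Plan, report prompted and spontaneous events separately. If a prompted item is already intended, this is a clarification only.
3. State that the rule on events judged caused by the intervention does not restrict the events compared between arms.
4. Make the Abstract and the Secondary Outcomes list agree on whether adverse events are a secondary outcome.

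The cost is one short item at three assessments, more non-serious events to review, and probably a higher reported event rate. According to Results, the research app is in development and testing until September 2027, and ethical approval is still to be sought, so the change can be made now. Harms that were not asked about cannot be fully recovered after launch.

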**Inclusion criteria**
Adults and adolescents aged 16 years or older (16 is the minimum age of consent without parental approval for participation in research in Norway. Inclusion of individuals aged younger than 18 years will be highlighted in the ethical review.)Residing in NorwayAccess to a compatible smartphone (iOS or Android)Reporting mild to moderately severe symptoms of anxiety and/or depression (Patient Health Questionnaire-9 [PHQ-9] score ≥5 and/or Generalized Anxiety Disorder-7 [GAD-7] ≥5)Able to read Norwegian and use Norwegian to a sufficient levelAble and willing to provide consent for the study prior to participation

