**Exclusion criteria (based on self-reporting)**
PHQ-9 score ≥20 (severe depression)Active suicidal ideation (PHQ-9 item 9 score ≥2)Have ever required hospitalization for mental illness or are currently taking antipsychotic or other psychotropic medicationsCurrent engagement in psychological treatmentReport having used Tankevirus or Grubl apps in the past

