#### Primary Outcomes

The co-primary outcomes in the trial are (1) the difference in the GAD-7 score for anxiety symptoms between baseline and postintervention for participants with mild to moderately severe self-reported problems with anxiety at baseline (GAD-7 score ≥5), and the difference in the PHQ-9 score for symptoms of depression between baseline and postintervention for participants with mild to moderately severe self-reported problems with depression at baseline (PHQ-9 score ≥5).

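### Severe anxiety (GAD-7 ≥15) triggers neither exclusion nor the Appendix 4 help information, although the appendix title names it as a ground for ineligibility

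*Protocol article*

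**What the plan says.** All references are to the protocol article.

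- **Severity bands.** Outcome Measurement Instruments gives the GAD-7 a range of 0 to 21 with cutoffs at 5, 10 and 15, the last labelled severe. PHQ-9 is severe from 20 and has an extra band, moderately severe, from 15.
- **Eligibility.** Textbox 1 includes people "Reporting mild to moderately severe symptoms of anxiety and/or depression", set as PHQ-9 ≥5 and/or GAD-7 ≥5. It excludes "PHQ-9 score ≥20 (severe depression") and item 9 scores of 2 or more. Current Level of Anxiety and Depression repeats these two upper limits. It uses GAD-7 only at the lower end: people are excluded "or if they report a total score ≤4 on both GAD-7 and PHQ-9".
- **Anxiety coprimary population.** Primary Outcomes describes the analysis as "for participants with mild to moderately severe self-reported problems with anxiety at baseline (GAD-7 score ≥5"), with no upper value.
- **Help information at screening.** The section on current and past health care use gives it to "Participants indicating severe depression (PHQ-9 ≥20) or responding with a score of ≥2 on PHQ-9 item 9, suggesting suicidal ideation". For everyone else who is turned away, "Individuals excluded based on other criteria will be provided with links to public information on mental health" and to the regular apps.
- **Help information in the app.** Safety Considerations adds a menu item "allowing users to report any discomfort and to optionally complete PHQ-9 and GAD-7 to report their current mental health". The recipients of the information are "Users indicating severe depression (PHQ-9 score ≥20) or reporting score ≥2 on item 9 of PHQ-9".
- **Help information during the trial.** Additional and Exploratory Analyses extends the same information to participants whose symptoms meet an exclusion criterion.
- **Appendix list.** The title of Multimedia Appendix 4 describes its readers as people found ineligible because of severe anxiety, depression or suicidal ideation.

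**The concern.** The appendix title presupposes a rule that does not exist. Nobody can be found ineligible for severe anxiety, because no exclusion criterion refers to a high anxiety score. The help information follows the exclusion criteria, so it has the same gap.

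The menu shows this most clearly. It collects a GAD-7 score from a user who is reporting discomfort, and then acts only on the PHQ-9 answers.

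Anxiety is a coprimary outcome, the trial is fully remote, and people from age 16 can enter. Safety Considerations itself accepts that the content or the self-monitoring might provoke anxiety in some users. The automated message therefore covers the severe band of one coprimary scale and not of the other, whether severe anxiety is present at entry or arises later in any arm. The ethics submission, still to be made, would also carry an appendix title that the eligibility criteria do not match.

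**Working it through.** The protocol states no figure to reproduce here. The check is one of rule logic.

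**Step 1: code the rules.** Let G be the GAD-7 total, P the PHQ-9 total and I the item 9 score.

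- Excluded on symptoms if P ≥ 20, or I ≥ 2, or (G ≤ 4 and P ≤ 4).
- Appendix 4 information at screening and in the menu if P ≥ 20 or I ≥ 2.
- Appendix 4 information during the trial if symptoms would exclude. On the high side this is again P ≥ 20 or I ≥ 2.

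G appears only in the lower-bound clause. The GAD-7 cut of 10 under Randomization and Blinding is a stratification factor and plays no part in eligibility or safety.

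**Step 2: enumerate the possible scores.** For each item 9 score from 0 to 3, the other eight PHQ-9 items add 0 to 24, so P takes 25 values. That gives 4 × 25 = 100 pairs (P, I). With 22 values of G there are 22 × 100 = 2200 combinations.

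- Combinations with G from 15 to 21: 7 × 100 = 700.
- Of these, with P < 20 and I < 2: for I = 0, P runs from 0 to 19 (20 values); for I = 1, P runs from 1 to 19 (19 values). So 7 × (20 + 19) = 273.
- Of the 273, excluded on symptoms: 0. Triggering the Appendix 4 information: 0.

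An extreme example is G = 21, P = 19, I = 1. This person has the maximum anxiety score, is eligible on symptoms and triggers nothing. The 273 are score patterns, not a share of participants.

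**Step 3: test both possible intentions.**

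| Sponsor's intention | Screening information | Menu | In-trial rule |
|---|---|---|---|
| GAD-7 ≥15 does not exclude (rules as written) | not triggered | not triggered | not triggered |
| GAD-7 ≥15 is added to the exclusion list only | not triggered; the person gets the links for other exclusion reasons | not triggered; PHQ-9 only | triggered by reference |

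The trigger gap does not depend on which intention is right, so the eligibility decision alone would not close it.

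**The case against.** The strongest reply is that the operative text is consistent. Textbox 1, the screening section, the screening information rule and the menu all give GAD-7 a lower bound only and set upper limits on PHQ-9 only. Against them stands one appendix title, for a text that is still a draft and is not shown. PHQ-9 triggers may be a deliberate choice, since they follow severe depression and suicidal ideation, and nothing in the document promises help information for every severe score. The app also carries helpline links whatever the score. Users get score feedback and can report events by menu, phone or email. Adverse events are reviewed weekly, and working-day monitoring escalates potential safety signals at once.

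Most of this stands as a limit on weight. It does not remove the conflict between the title and the criteria, and no section ties any of the other channels to a GAD-7 value. The sponsor added a score-triggered message for severe depression despite the helpline links, and the document gives no reason for treating severe anxiety differently.

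Three stronger readings are tempting but not supported:

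- **That Risk Management and Participant Safety promises exclusion for severe anxiety.** Its sentence on severe symptoms follows one on suicidality and does not name anxiety. It may only summarise the PHQ-9 rules.
- **That the population wording is a competing rule.** Moderately severe is a PHQ-9 band, and the criteria define the phrase by scores of 5 or more. The mild to moderate wording under Aim, Design, and Setting fits GAD-7 ≥15 badly, but it fits the admitted PHQ-9 scores of 15 to 19 just as badly.
- **That a known, sizeable share of participants is affected or left without help.** The protocol gives an assumed correlation of about 0.7 between the scales but no means or standard deviations, so no share can be derived. The helpline links reach everyone.

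**Conclusion.** The point holds as a mismatch between the Appendix 4 title and the operative criteria, together with a gap in the safety triggers. Every score pattern with GAD-7 15 to 21, PHQ-9 below 20 and item 9 below 2 is eligible on symptoms and never prompts the Appendix 4 information, even when the GAD-7 score is reported through the menu built for that purpose.

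The number of people concerned is unknown. What they lose is also uncertain, because the Appendix 4 text is not shown and how much it adds to the helpline links cannot be judged. The document does not reveal whether an upper GAD-7 limit was forgotten or severe anxiety is meant to be enrolled.

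The conclusion rests on reading the three stated routes to Appendix 4 as the only ones. The trigger gap has no shown effect on the primary analysis, power or type I error. It should be corrected before the app is programmed, because the correction is cheap and serves participant safety.

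**What to change.** 1. Add GAD-7 ≥15 as an automated trigger for the Appendix 4 information in three places: the screening rule (the section on current and past health care use), the report menu (Safety Considerations) and the in-trial rule (Additional and Exploratory Analyses). Apply it identically in all three arms, at screening, in the menu, and at the postintervention, 3-month and 6-month assessments. Include text in Appendix 4 that suits severe anxiety.
2. Separately, have the sponsor state whether GAD-7 ≥15 excludes. Then align Textbox 1, Current Level of Anxiety and Depression and the Appendix 4 title with that decision, along with the population wording under Aim, Design, and Setting, Inclusion and Exclusion Criteria, and Primary Outcomes. If severe anxiety is to be enrolled, the title should no longer call it a ground for ineligibility.

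**Cost.** The first change is one rule on data already collected, in an app still to be finished and before ethics approval, plus short wording changes. It adds one automated message and slightly more signposting to outside care in every arm, which the planned co-treatment and resource use questions would record. If the sponsor chooses exclusion, the recruitment pool also shrinks, by a share the protocol does not allow one to estimate.
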